## 10.2 Central measurement inspection

When conducting routine blood sampling at the start of treatment, at 12 weeks, and at 96 weeks, collect blood for central measurement inspection and high-sensitivity CRP, folic acid, vitamin B12, NT-proBNP, serum iron, ferritin, and TIBC. An 18 mL sample of blood (approximately 6 mL of serum) is needed for this measurement. Sample collection and measurement will be conducted at SRL Medisearch Inc. (henceforth, “SRL”). The study physician records the inspection results from the inspection company in the case report form. Procedures, such as sample collection for central batch measurements, are specified separately in the SRL standard operating procedure.

Samples collected by the central batch measurement inspection will be stored according to the SRL standard operating procedure after measurements are completed, after which they are to be stored for 10 years. Samples should be discarded after the end of the storage period. Additionally, if items requiring inspection are added following the start of the study, then the stored samples will be used for measurement after obtaining the approval of the principal investigator-affiliated facility, the Foundation for the Promotion of Advanced Medicine, and the ethical review committee of the research sponsor. The lead principal physician and study physician also obtain consent for sample storage and additional measurements with stored samples when consent is obtained from the patient for research participation.

## 10.3 Observation / inspection / reporting schedule

Observations, investigations, and inspections are conducted according to the following.

| Item \ Time                                                                                             | Registration | Prior to start of treatment | Observation period                                                                   |                      |          |          |          |          |          |          |          |          |          |          | Simultaneous outcome | Discontinuation of participation / with drawal of consent |
|---------------------------------------------------------------------------------------------------------|--------------|-----------------------------|--------------------------------------------------------------------------------------|----------------------|----------|----------|----------|----------|----------|----------|----------|----------|----------|----------|----------------------|-----------------------------------------------------------|
|                                                                                                         |              |                             | Start of treatment                                                                   | 2, 4, 6, 8, 10 weeks | 12 weeks | 16 weeks | 20 weeks | 24 weeks | 28 weeks | 32 weeks | 36 weeks | 40 weeks | 44 weeks | 48 weeks |                      |                                                           |
| Eligibility determination                                                                               |              |                             |                                                                                      |                      |          |          |          |          |          |          |          |          |          |          |                      |                                                           |
| Primary disease / complications / medical history                                                       |              | ○                           |                                                                                      |                      |          |          |          |          |          |          |          |          |          |          |                      |                                                           |
| PWV *1                                                                                                  |              | ○                           |                                                                                      |                      |          |          |          |          |          |          |          |          |          |          |                      |                                                           |
| 12-lead electrocardiogram / chest X-ray                                                                 |              | ●                           |                                                                                      |                      |          |          |          |          |          |          |          |          |          |          |                      |                                                           |
| Height                                                                                                  |              | ○                           |                                                                                      |                      |          |          |          |          |          |          |          |          |          |          |                      |                                                           |
| Weight                                                                                                  |              |                             | ○                                                                                    | ○                    | ○        | ○        | ○        | ○        | ○        | ○        | ○        | ○        | ○        | ○        |                      |                                                           |
| Blood pressure                                                                                          |              |                             | ○                                                                                    |                      | ○        |          | ○        |          | ○        |          | ○        |          | ○        |          |                      |                                                           |
| Urinalysis: urine protein, urine Cr, PCR                                                                |              |                             | ○                                                                                    |                      | ○        |          |          |          | ○        |          |          |          | ○        |          |                      |                                                           |
| Blood test: HbA1c (only for diabetic patients) *2                                                       |              |                             | ○                                                                                    |                      |          |          |          |          |          |          |          |          |          |          |                      |                                                           |
| Blood test: Hb, MCV, Cr, eGFR, Alb, serum iron, ferritin, TIBC                                          |              |                             | ○                                                                                    | ○                    | ○        | ○        | ○        | ○        | ○        | ○        | ○        | ○        | ○        | ○        |                      |                                                           |
| Blood test (central measurement): high-sensitivity CRP, folic acid, VB12, NT-proBNP, Fe, ferritin, TIBC |              |                             | ★                                                                                    |                      | ★        |          |          |          |          |          |          |          |          | ★        |                      |                                                           |
| Darbepoetin alfa administration status                                                                  |              |                             | [figure not shown] |                      |          |          |          |          |          |          |          |          |          |          |                      |                                                           |

|                                             |                                                                                             |   |   |         |   |   |   |          |   |   |   |   |   |         |  |   |
|---------------------------------------------|---------------------------------------------------------------------------------------------|---|---|---------|---|---|---|----------|---|---|---|---|---|---------|--|---|
| Iron formulation usage status               |                                                                                             |   |   |         |   |   |   |          |   |   |   |   |   |         |  |   |
| Miscellaneous concomitant drug usage status |                                                                                             |   | ○ | ○       | ○ | ○ | ○ | ○        | ○ | ○ | ○ | ○ | ○ | ○       |  |   |
| Blood transfusion status                    |                                                                                             |   | ○ | ○       | ○ | ○ | ○ | ○        | ○ | ○ | ○ | ○ | ○ | ○       |  |   |
| Anemia influencing factor information       |                                                                                             |   | ○ | ○       | ○ | ○ | ○ | ○        | ○ | ○ | ○ | ○ | ○ | ○       |  |   |
| Events / adverse events                     |                                                                                             |   |   |         |   |   |   |          |   |   |   |   |   |         |  |   |
| Outcome information                         |                                                                                             |   |   |         |   |   |   |          |   |   |   |   |   |         |  |   |
| Discontinuation / consent withdrawal        |                                                                                             |   |   |         |   |   |   |          |   |   |   |   |   |         |  | ○ |
| Inspection content                          |                                                                                             |   | 0 | ±1 week |   |   |   | ±6 weeks |   |   |   |   |   | 4 weeks |  |   |
| Case report form submission deadline        | ☆                                                                                           | ☆ |   |         | ☆ | ☆ | ☆ |          | ☆ |   | ☆ |   | ☆ | ☆       |  |   |
|                                             | After registration or within four weeks of end of final inspection of each case report form |   |   |         |   |   |   |          |   |   |   |   |   |         |  |   |

○ : Required

● : Implement before the start of treatment if there are no inspection results within 12 weeks prior to registration. Do not record in the case report form; report when an event occurs at the request of the event evaluation committee.

◇ : Implement only for Hb, Cr, eGFR (when inspection is implemented within eight weeks prior to registration, its latest value is allowed).

★ Central measurement: collect blood prior to darbepoetin alfa administration.

\*1: Report the latest inspection values from 12 weeks prior to registration to five weeks after registration.

\*2: Report the latest inspection values from eight weeks prior to treatment to start of treatment.

#### 10.4 Definition of criteria related to observation / inspection / report items

##### 10.4.1 Event

The following renal function deterioration or CVD events are set as events in this study. These definitions are provided separately.

|                              |                                                                                                                                                                                                                                                                                                                                                                                                                                                                                                                                                                                                                                                                                                                                                                                                                                                                                                                                                                                                                                                                                                                                                     |
|------------------------------|-----------------------------------------------------------------------------------------------------------------------------------------------------------------------------------------------------------------------------------------------------------------------------------------------------------------------------------------------------------------------------------------------------------------------------------------------------------------------------------------------------------------------------------------------------------------------------------------------------------------------------------------------------------------------------------------------------------------------------------------------------------------------------------------------------------------------------------------------------------------------------------------------------------------------------------------------------------------------------------------------------------------------------------------------------------------------------------------------------------------------------------------------------|
| Renal function deterioration | 
① Initiation of maintenance dialysis, ② kidney transplantation, ③ 50% decrease in eGFR, ④ eGFR less than or equal to 6mL/min/1.73 m^2
 
< Supplement >
The eGFR decline rate is calculated with the average eGFR value from the start of treatment to up to 12 weeks as the baseline.
 
The first point where decreases are observed at three consecutive points is used for ③ 50% decrease in eGFR and ④ eGFR less than or equal to 6mL/min/1.73 m^2
                                                                                                                                                                                                                                                                                                                                                                                                                                                                                                                                                                                                                                                |
| CVD event                    | 
Fatal
 
① Death due to myocardial infarction, ② sudden death, ③ death due to congestive heart failure, ④ death due to arrhythmia, ⑤ cerebrovascular death, ⑥ death due to aortic dissection, ⑦ death due to ischemia of major organs other than the heart / brain, ⑧ other forms of cardiovascular disease
 
Non-fatal
 
① Myocardial infarction*1, ② hospitalization due to angina pectoris, ③ hospitalization for ischemic heart disease requiring invasive intervention treatment, ④ hospitalization for congestive heart failure with chronic organic heart disease*2 (excluding arrhythmia), ⑤ hospitalization for severe arrhythmia and atrial fibrillation / atrial flutter, ⑥ hospitalization due to cerebrovascular disease, ⑦ hospitalization due to chronic arteriosclerosis obliterans, ⑧ hospitalization due to aortic dissection, ⑨ hospitalization due to ischemia of major organs other than the heart / brain
 
*1: New-onset (asymptomatic) myocardial infarction is treated as an event even without hospitalization.
*2: Includes old myocardial infarction, valvular disease, epicarditis, etc.
 |

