#### 9.1.2 Definition of serious adverse events

The following are referred to as serious adverse events.

- (1) Death
- (2) Injury
- (3) Risk of death
- (4) Risk of injury
- (5) Hospitalization or its extension due to treatment
- (6) Serious events relating to above-mentioned (1)–(5) (other medically important conditions)
- (7) Congenital disorders or abnormalities in later generations

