| 10* | Event
Note) refer to attachment for definition           | Event name
CVD event                                                                                                                                                                                                                                               | Fatal                                                                                                                                                                     | Death due to myocardial infarction, sudden death, congestive heart failure, arrhythmia, cerebrovascular death, aortic dissection, ischemia of major organs other than the heart / brain, or other types of cardiovascular death                                                                                                                                                                                                |
|     |                                                             |                                                                                                                                                                                                                                                                       | Non-fatal                                                                                                                                                                 | Myocardial infarction*1, hospitalization due to angina pectoris, ischemic heart disease requiring invasive intervention treatment, congestive heart failure with chronic organic heart disease*2 (excluding arrhythmia), severe arrhythmia and atrial fibrillation / atrial flutter, cerebrovascular disease, chronic arteriosclerosis obliterans, aortic dissection, or ischemia of major organs other than the heart / brain |

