#### 12.1.2 CVD event

Composite events of each event occurring 12 weeks after the start of treatment are set as the CVD event. The number of days until occurrence is calculated, with 12 weeks after the start of treatment as the starting point.

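### Section 10.4.1 counts non-fatal CVD events other than myocardial infarction only as hospitalizations and is silent on onset during an existing stay, while the event lists in 10.1.3 to 10.1.5 set no such condition for most of them

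*Protocol*

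**What the plan says.** Section 12.1.2 makes CVD one of the two primary endpoints: "Composite events of each event occurring 12 weeks after the start of treatment are set as the CVD event". Section 10.4.1 lists the events. Non-fatal item 1 is myocardial infarction. Items 2 to 9 are all worded as hospitalization due to, or for, a condition. Item 4 is "hospitalization for congestive heart failure with chronic organic heart disease", item 5 is "hospitalization for severe arrhythmia and atrial fibrillation / atrial flutter" and item 6 is "hospitalization due to cerebrovascular disease". The one stated exception is a footnote to item 1: "New-onset (asymptomatic) myocardial infarction is treated as an event even without hospitalization". Onset during an existing stay and prolongation of a stay are not mentioned. The section's introduction adds: "These definitions are provided separately".

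The event lists in 10.1.3, 10.1.4 and 10.1.5, which say what is entered on the case report form, print the same conditions differently. Only angina carries the word hospitalization. The rest are bare conditions, for example "severe arrhythmia and atrial fibrillation / atrial flutter, cerebrovascular disease, chronic arteriosclerosis obliterans, aortic dissection". All three lists repeat the infarction footnote, refer to an attachment for definitions, and ask for an onset date.

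For serious adverse events, section 9.1.2 does cover a longer stay: "Hospitalization or its extension due to treatment".

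**The concern.** Take a patient admitted for an infection who has a stroke on day 3 and survives. The admission was not due to cerebrovascular disease, so item 6 is not met as printed. If the patient dies of the stroke, fatal item 5 applies and the event counts. Whether the same in-hospital event enters the composite therefore depends on survival. It would also be a serious adverse event if it prolonged the stay, yet not a CVD event.

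The site, meanwhile, completes a list in which cerebrovascular disease appears without any admission condition. One site may enter the stroke as a CVD event and another may not, each following a part of the protocol.

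The CVD endpoint feeds the proportional hazards model, the time-dependent ROC curves, the ERI cut-offs and the Kaplan-Meier comparison in section 13.3.1. An unclear event definition runs through all of these.

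**Working it through.** **1. The two definitions side by side**

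| Non-fatal item | 10.4.1 | Lists in 10.1.3, 10.1.4, 10.1.5 |
|---|---|---|
| 1 Myocardial infarction | No admission needed | No admission needed |
| 2 Angina | Admission | Admission |
| 3 Ischaemic heart disease with intervention | Admission | Not stated |
| 4 Heart failure | Admission | Not stated |
| 5 Severe arrhythmia, atrial fibrillation/flutter | Admission | Not stated |
| 6 Cerebrovascular disease | Admission | Not stated |
| 7 Arteriosclerosis obliterans | Admission | Not stated |
| 8 Aortic dissection | Admission | Not stated |
| 9 Ischaemia of other major organs | Admission | Not stated |

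Seven of the nine items differ. Section 12.1.2 does not settle which list governs: it refers to each event without citing 10.4.1, whereas 12.1.1 does cite it for the renal endpoint.

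**2. The plan's own event count, for scale**

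Section 13.1 gives 2,000 patients, two years and 13.1 events per 100 person-years.

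- Expected events: 2,000 × 2 × 0.131 = 524.
- 95% interval: 524 ± 1.96 × √524 = 479.1 to 568.9, which matches the stated 480–568.

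The protocol gives no share of CVD events that are non-fatal, are not infarction, and begin in hospital. Under assumed shares of all events:

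| Assumed share | Events in doubt (524 × share) | Left |
|---|---|---|
| 2% | 10 | 514 |
| 5% | 26 | 498 |
| 10% | 52 | 472 |
| 15% | 79 | 445 |

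**3. Effect on a comparison of ERI groups**

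Let *a* be the share of composite events that fall under items 2 to 9, taken as equal in both groups. Let *H* and *L* be the shares of those events not counted in the high- and low-ERI groups. Then

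observed ratio = true ratio × (1 − *aH*) / (1 − *aL*).

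Fatal events and infarction are unaffected, so *a* is below 1. All values here are assumptions: *a* = 0.6 for illustration, and *a* = 1 as the limit in which no event is fatal or an infarction. With *L* = 5%:

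| *H* | True 1.5, *a* = 0.6 | True 1.5, *a* = 1 | True 2.0, *a* = 0.6 | True 2.0, *a* = 1 |
|---|---|---|---|---|
| 5% | 1.50 | 1.50 | 2.00 | 2.00 |
| 10% | 1.45 | 1.42 | 1.94 | 1.89 |
| 15% | 1.41 | 1.34 | 1.88 | 1.79 |
| 20% | 1.36 | 1.26 | 1.81 | 1.68 |

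Example: 1.5 × (1 − 0.6 × 0.20) / (1 − 0.6 × 0.05) = 1.5 × 0.88 / 0.97 = 1.36.

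Equal loss leaves the ratio unchanged and costs events only: at 10% in both groups and *a* = 0.6, that is 6% of the composite. If the loss were greater in the low-ERI group (20% against 5%), a true 1.5 would appear as 1.5 × 0.97 / 0.88 = 1.65. The direction therefore follows entirely from an assumption that the protocol does not supply.

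**The case against.** The strongest reply is that 10.4.1 is a list of event names. The operative definitions are in an attachment that is not shown, and it may already deal with in-hospital onset. Section 16.3 also sets up an event evaluation committee with its own manual. And because the event lists carry no admission condition for most items, an in-hospital stroke can be recorded. All of this stands against the inference, which a reader might draw, that such events are lost from the endpoint. The documents do not show that. They show only that the event does not meet 10.4.1 as printed. The reply does not clear the text, however. An attachment that dropped the admission requirement would contradict 10.4.1, and section 16.3 does not say that the committee may waive it.

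A second reply is that the word hospitalization before angina in the lists was meant to carry forward to the later items; the repeated infarction footnote fits that reading. If so, the conflict disappears, but the gap for in-hospital onset then runs through all four sections.

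Third, hospitalization for a condition (items 3 to 5) could be read to include a stay continued because of it. That is possible for those three items, but less natural for the other five, which say due to.

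Fourth, requiring admission is a legitimate severity threshold in an exploratory study with no hypothesis to verify (section 13.3). This is accepted, and covering in-hospital onset and prolongation does not remove the threshold.

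A reader might also infer that the ERI-CVD association is diluted, because section 2 names infection and bleeding among the causes of low ESA response and these also lead to admission. That is plausible, but no passage relates in-hospital onset to ERI, and obvious hemorrhagic lesions are excluded at entry.

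**Conclusion.** The point holds as a defect of definition. As printed, 10.4.1 leaves out non-fatal CVD events other than infarction that begin during an admission for another cause, while the fatal counterparts count. For seven of nine items the event lists differ from 10.4.1 on whether admission is required. Both affect a primary endpoint.

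The size is unknown. The range of 10 to 79 events rests on assumed shares of 2% to 15%. A bias in the ERI comparison needs loss that differs by ERI group, which is not shown; any dilution of the composite would be smaller than a calculation that applies the loss to every event, because fatal events and infarction are kept. The sample size figure in section 13.1 reproduces and is not called into question. The correction is worth making because it is cheap and removes site-to-site differences in what is reported.

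**What to change.** - In 10.4.1, word items 2 to 9 as: hospitalization, or onset during or prolongation of an existing hospitalization, due to the condition.
- Use the identical wording in the event lists of 10.1.3, 10.1.4 and 10.1.5 and in the separate definitions attachment.
- Cite 10.4.1 in 12.1.2, as 12.1.1 already does for the renal endpoint.
- State that the event date is the onset date, which the three lists already collect with date of initial diagnosis as the fallback.

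The cost is a text and form change, with no added visits or tests. Whether a stay was prolonged needs a judgement, which can go to the existing event evaluation committee. Serious adverse event reports should not be relied on alone to recover these events: section 9.4.1 limits mandatory reporting to 30 days after darbepoetin alfa ends, while section 8.2 keeps patients who stop the drug under observation to week 96.
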